### Adherence

Medication adherence is assessed at each medication check-in using capsule counts and self-report. At each medication check-in visit, medication instructions are reviewed with the participant and strategies to support adherence are discussed. To further increase medication adherence, a text message is sent out daily reminding participants to take their study medication. To ensure participant privacy and to accommodate those who may not wish to disclose their involvement in a research study or share their phones, the message reads: “Please remember GRAIL.” Participants are able to reduce the frequency to 2 days per week or opt out of text message reminders entirely at any time throughout the study.

### Study outcomes

The primary outcome is undetectable HVL (< 200 copies/ml) at 3 months, with secondary outcomes being undetectable HVL at 6 and 12 months. In order to explore potential mechanisms by which gabapentin may lead to HVL suppression, we assess the impact of gabapentin compared to placebo on the following secondary outcomes: a) alcohol consumption; b) pain severity; c) ART adherence; and d) engagement in HIV care.

### Questionnaires

Participants are assessed at baseline, 3, 6, and 12 months post enrollment, along with shorter medication visits by phone at weeks 1, 3, 6 and 10 and shorter medication visits in-person at weeks 2, 4 and 8. All follow-up study visits take place at the clinic from where the participant was recruited or by phone.

Participants receive a meal at each study visit, along with either 1 kg of rice and one bar of soap, or two bars of soap, as compensation. Transport costs are also reimbursed: 20,000 UGX (5.33 USD) for those living within 20 km, 30,000 UGX (8 USD) for 20–40km, and up to 45,000 UGX (12 USD) for 40–60km from the study site.

The study has employed a driver to provide transportation to the clinic for participants who require a ride to their study visit appointments.

### Questionnaires

Components of the baseline and follow-up assessments are listed in Table 3. At each in-person study visit, RAs measure and record participants’ weight and blood pressure. Height is measured at the baseline visit. Over the course of the study, we review medical charts to obtain HIV treatment history. Participants are asked to provide consent so that their data may be used for potential future ancillary studies.

### Laboratory testing and results

Blood is collected throughout the study. CD4 count and creatinine are tested at baseline. Phosphatidylethanol (PEth, an alcohol biomarker) [13], is tested at baseline and 3 months. HIV viral loads are tested at 3, 6, and 12 months. Participants with a creatinine clearance of < 60mL/min have their study medication dose reduced per clinical recommendations for prescribing gabapentin for patients with chronic kidney disease. Additionally, at the 3-month study visit, all participants are asked to provide blood for an HIV drug resistance test, however the test is only conducted for those with a detectable HVL at 3 months to assess if the HIV is resistant to that participant’s ART regimen.

Urine samples are collected during screening to test for pregnancy and alcohol use, the latter by using an ethyl glucuronide (EtG) dip test. An EtG dip test is a type of urine test used to detect the presence of alcohol. In this study, we use a test with an 80-hour detection window and a 300 ng/mL cutoff. Additionally, urine is collected for women during in-person medication check-ins and at 3 months to confirm the participant is not pregnant. Participants found to be pregnant will discontinue their study medication but will continue follow-up assessments for the duration of the study.

### Retention of study participants

Participants are asked to provide contact information for 2–3 alternative contacts (e.g., friends and family) who can assist in the event of being lost to follow-up. Efforts to improve retention for all participants include the provision of refreshments during study visits, reimbursements for travel expenses, and conducting home visits when necessary.

### Adverse events and safety monitoring

At baseline, participant symptoms are assessed to document any chronic conditions or symptoms that existed prior to the introduction of study medication. These are documented on the baseline event form and are reviewed and compared to reported adverse events throughout the study. During follow-up, symptoms are assessed weekly for the first month, and biweekly thereafter while the participants are administered study medication. If a participant experiences a severe or medically significant but not immediately life-threatening symptom, the RA increases monitoring frequently for safety, and the team considers adjusting the medication dose or stopping it. Participants may be unblinded if there is an urgent medical need, as determined by the clinician evaluating the participant. If a participant is unblinded, study medication may be discontinued if deemed medically necessary.

Any event that meet the criteria for an adverse event (AE), serious adverse event (SAE), or unanticipated problem is recorded. All events are reviewed by a study physician. AEs and SAEs are periodically presented to and reviewed by an external Data and Safety Monitoring Board (DSMB), the IRBs, and the Uganda’s National Drug Authority.

### Data management

The Biostatistics and Epidemiology Data Analytics Center at Boston University provides statistical collaboration in the design and analysis of the GRAIL trial. Electronic questionnaires include programmed skip patterns and range checks, minimizing errors at data capture. Participant screening, assessment, tracking, and randomization utilize Research Electronic Data Capture (REDCap) mobile.

### Analytic methods

The study uses an intention-to-treat analysis that includes all participants according to their randomized assignment. Descriptive statistics are calculated for variables at baseline and each follow-up time to assess whether there appear to be any differences across treatment arms. Spearman correlation analyses are performed to identify pairs of variables that may be collinear. In addition, the variance inflation factor is assessed to detect possible collinearity.

The primary outcome for this study is undetectable HVL (< 200 copies/ml) at 3 months. The primary analysis uses multivariable logistic regression analyses to control for the randomization stratification factors to improve efficiency (i.e., AUDIT > 20, clinic site). If any baseline factors appear to differ by randomized group, additional sensitivity analyses will be conducted controlling for these factors to assess for potential confounding. Other binary outcomes (e.g., heavy alcohol consumption [defined as PEth ≥ 50 ng/mL], adherence to ART [defined as taking ≥ 80% of prescribed medication via Visual Analog Scale], engagement in HIV care [defined as ≥ 1 HIV visit in the past 3 months]) will be analyzed using the same approach. Number of heavy drinking days (assessed using the Timeline Followback [TLFB] method) in the past month will be analyzed using negative binominal regression, to account for overdispersion in the data. Percentage of ART pills taken (assessed by self-report), a continuous outcome, will be analyzed using multiple linear regression if the data are normally distributed. However, if the distribution is skewed, transformations of the data will be performed (e.g., log transformation). If an appropriate transformation is not identified, a median regression model will be used. A secondary analysis will be conducted using a per protocol approach that includes only those participants who were adherent to their assigned intervention (i.e., defined as taking at least 80% of the assigned medication), as determined by self-report (i.e., Visual Analog Scale).

Given the repeated measures of our primary outcome (i.e., 3, 6, and 12 months), additional exploratory analyses using longitudinal regression models will be used to incorporate repeated measures for each outcome in the same model and will test for possible gabapentin by time interactions. For the dichotomous undetectable HIV viral load outcome, we will use generalized estimating equations (GEE), with an autoregressive working correlation matrix, a logit link; standard errors will be based on the empirical-sandwich estimator. Longitudinal analyses of heavy alcohol consumption will be analyzed using the same approach. For number of heavy drinking days, we will use GEE negative binomial regression models. For continuous outcomes, such as percentage of ART taken, we will use generalized linear mixed effects models that include subject-specific random intercepts and slopes to account for the correlation due to having repeated observations from each subject.

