**Methods::**

To describe the protocol for arandomized, double-blinded, placebo-controlled trial, (GRAIL [Gabapentin to Reduce Alcohol and Improve viral Load suppression]), to test the efficacy of gabapentin versus placebo on achieving undetectable HIV viral load among people with HIV with risky drinking. We recruit and randomize 300 people with detectable HIV viral loads (>= 200 copies/ml) and risky drinking. Participants are randomized 1:1 to receive either gabapentin (1800 mg/day target dose) or placebo for 3 months in a double blind design. Both arms receive a 5-minute evidence-based counseling session aimed at reducing alcohol use. The primary outcome is undetectable viral load (<200 copies/ml) at 3 months. Other secondary outcomes include undetectable viral load at 6 and 12 months, biomarker-confirmed recent alcohol consumption, antiretroviral therapy (ART) adherence, engagement in HIV care and pain severity. This study takes place in Mbarara, Uganda, as the country ranks among the top five for alcohol consumption globally and has 1.4 million people living with HIV.

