### Sample size, power, and effect size

We present power calculations for the primary outcome HVL suppression at 3 months post randomization. The calculations assume an alpha level of 0.05 and that 300 participants are enrolled into the trial. The GRAIL trial was initially designed to be conducted in Russia, with our sample size justification derived from prior research conducted among the Russian population. Based on data from our previous study of Russian people with HIV and risky drinking [14], we expect 40% of control participants will have undetectable HVL at 3 months. Given this and assuming 15% loss to follow-up at 3 months (i.e., 255 evaluable subjects) the study will have 80% power to detect an absolute difference of 19% in the proportions with undetectable HVL at 3 months (i.e., 59% vs. 40% in the gabapentin and control arms, respectively) using a chi-square test with continuity correction. We anticipate larger effects may be observed in the GRAIL trial, which would result in even higher power. In the Russian study, among participants on ART who reduced alcohol consumption, approximately 76% had HVL suppression at the 3-month follow-up. If a similar proportion achieves HVL suppression in the gabapentin arm, the study would have > 99% power to detect this 36% difference between randomized groups (i.e., 76% vs. 40% in the gabapentin and control arms, respectively). The trial is adequately powered to detect differences between arms as small as 19%, which are still considered clinically meaningful.

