**Inclusion Criteria**
18 years or older
Having an HIV diagnosis for at least 6 months (assessed via medical charts)
Current (within 2 months) detectable HIV viral load at least 6 months after HIV diagnosis (assessed via medical charts or study test)
Positive Ethyl Glucuronide (EtG) urine test (300 ng/ml cutoff)
Able and willing to comply with all study protocols and procedures
Living within 2 hours travel time of the study site

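### Free improvement: the primary logistic model could also adjust for the qualifying HIV viral load, which eligibility requires of every participant

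*Protocol article*

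**What the plan says.** All references are to the protocol article.

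- **Outcome** (Analytic methods): "The primary outcome for this study is undetectable HVL (< 200 copies/ml) at 3 months".
- **Primary model** (Analytic methods): "The primary analysis uses multivariable logistic regression analyses to control for the randomization stratification factors to improve efficiency". The factors are then spelled out as "i.e., AUDIT > 20, clinic site", which reads as a complete list.
- **Other baseline variables** (Analytic methods): "If any baseline factors appear to differ by randomized group, additional sensitivity analyses will be conducted controlling for these factors".
- **Entry requirement** (Table 1, Inclusion Criteria): "Current (within 2 months) detectable HIV viral load at least 6 months after HIV diagnosis (assessed via medical charts or study test". The abstract gives the threshold, describing the trial population as "people with detectable HIV viral loads (>= 200 copies/ml) and risky drinking".
- **Study viral load tests** (Laboratory testing and results): "HIV viral loads are tested at 3, 6, and 12 months".
- **Power** (Sample size, power, and effect size): "The calculations assume an alpha level of 0.05 and that 300 participants are enrolled into the trial". With 15% loss, 255 are evaluable. The stated result is 80% power for 59% versus 40%, by a chi-square test with continuity correction and no covariates.

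**The concern.** The stated reason for covariate adjustment is efficiency, and the Randomization section justifies the AUDIT stratum on prognostic grounds: heavier drinkers may be less likely to suppress. The same reasoning points to starting viral load. One threshold, 200 copies/ml, marks both entry and success, so distance above it is an obvious candidate predictor of falling below it 3 months later. Viral load is neither a stratification factor nor in the primary model.

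The sensitivity analyses do not fill the gap. They bring in a baseline factor only when the arms appear to differ on it, whereas the benefit of adjustment depends on how prognostic the factor is. At stake is some power on the primary outcome, obtainable without extra participants or visits.

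**Working it through.** **1. The plan's own figure.** Inputs from the sample size section: p0 = 0.40, p1 = 0.59, alpha 0.05 (two-sided assumed; not stated), 300 × 0.85 = 255 evaluable, so n = 127.5 per arm.

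- Difference less continuity correction: 0.19 − 1/127.5 = 0.1822.
- Null SE, pooled p = 0.495: √(2 × 0.495 × 0.505 / 127.5) = 0.0626.
- Alternative SE: √((0.40 × 0.60 + 0.59 × 0.41) / 127.5) = 0.0615.
- z = (0.1822 − 1.96 × 0.0626) / 0.0615 = 0.967, so power = 83.3%.

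Exact enumeration of the corrected test (127 versus 128) gives 82.4%; without correction the formula gives 86.3%. A difference of 18 points gives 78.9%, so 19 is the smallest whole-point difference with at least 80% power. The stated 80% is conservative rounding.

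**2. Adding the qualifying viral load.** The article gives no prognostic strength, so it was varied. Trials of 255 participants (127 and 128) were simulated, 3,000 per setting, with a standard normal covariate standing for log viral load. Marginal rates were held at 40% and 59%. A logistic model with arm alone was compared with one that also contained the covariate (Wald test, two-sided 0.05). AUDIT stratum and clinic were not simulated. Monte Carlo error is about 1 point.

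| Assumed odds ratio per SD | Power without | Power with | Relative efficiency, standardised risk difference |
|---|---|---|---|
| 1.0 | 85% | 85% | 1.00 |
| 1.25 | 85% | 86% | 1.01 |
| 1.5 | 86% | 88% | 1.01 |
| 2.0 | 85% | 89% | 1.09 |
| 2.5 | 85% | 91% | 1.21 |
| 3.0 | 85% | 92% | 1.26 |

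The odds ratios are per SD in the direction of lower viral load favouring suppression. Relative efficiency is the variance of the raw risk difference divided by that of the standardised one. A value of 1.09 equates to 255 × 1.09 ≈ 278 evaluable participants, and 1.26 to 255 × 1.26 ≈ 321.

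**3. Where the gain lies.** At an odds ratio of 2.0 per SD, the mean treatment log odds ratio goes from 0.777 to 0.862 and its SE from 0.256 to 0.273. The ratio moves from 0.777 / 0.256 = 3.04 to 0.862 / 0.273 = 3.16. The SE rises, but the conditional effect moves further from zero by more, so power increases.

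**4. Scale of the target.** The target is an absolute difference of 0.59 − 0.40 = 19 points. The same rates give an odds ratio of (0.59/0.41) / (0.40/0.60) = 2.16 and a risk ratio of 0.59/0.40 = 1.48. A risk difference would therefore speak directly to the power statement.

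**The case against.** The strongest reply is that adjusting for the stratification factors is a sound primary analysis and nothing here makes it wrong. That stands. A reader might infer several stronger things that the article does not support.

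- **That the primary result would be biased or the trial underpowered.** Randomisation protects the comparison, and the power recomputed without the covariate is 82% to 86%, above the stated 80%.
- **That the loss is certain.** The article says nothing on how well the qualifying value predicts suppression. It may be up to 2 months old and may come from a chart or a study test, which could weaken it. A nil gain is within the range. Since AUDIT stratum and clinic were not simulated, any information they share with viral load is credited to viral load here.
- **That adjustment sharpens the log odds ratio.** Its SE increases, as shown.
- **That the data choose the primary covariates.** Imbalance-triggered adjustment is already confined to sensitivity analyses and needs no change.
- **That naming a logistic model contradicts an absolute target.** It does not. Effect measures may be left to the analysis plan, which is not shown.
- **That no baseline viral load is taken.** The laboratory section lists none, but Table 3 and Figure 2 are not in the available text.

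It is also fair that eligibility guarantees a detectable result, not that its number and date are held in the trial database.

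The core survives: the covariate list is closed, the omitted variable is the outcome measured before randomisation, and a prespecified baseline covariate is valid whatever its strength.

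**Conclusion.** This is an optional improvement, not a fault. The primary model seeks efficiency but leaves out the qualifying viral load. The possible gain runs from nil to about 7 points of power (85% to 92%), and from 1.00 to 1.26 in relative efficiency of a standardised risk difference, across assumed odds ratios of 1.0 to 3.0 per SD. At 1.5 or below, the power gain is 0 to about 2 points. The figures rest on the article's rates and evaluable number, a two-sided 0.05 test, a normally distributed log viral load and no contribution from AUDIT stratum or clinic.

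**What to change.** Before unblinding, prespecify in the analysis plan:

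- log10 of the most recent pre-randomisation viral load, from chart or study test, as a covariate in the primary logistic model alongside AUDIT stratum and clinic site;
- optionally, days from that test to randomisation (its effect was not simulated);
- a simple rule for any missing numeric value;
- a covariate-standardised risk difference with 95% CI from the same model, reported beside the odds ratio.

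The Trial status section expects recruitment to finish in May 2026 and the trial is double-blind, so a change made before unblinding would not be informed by results by arm. No new visits or tests are needed. The costs are extracting the numeric result and test date where they are not already recorded, and accepting a conditional odds ratio that differs slightly from the one the current model estimates.

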## Methods

GRAIL is a randomized, double-blinded, placebo-controlled clinical trial designed to evaluate the efficacy of gabapentin versus placebo in achieving undetectable HVL in 300 PWH who engage in recent risky drinking. Risky drinking is operationalized as a positive Alcohol Use Disorders Identification Test - Concise (AUDIT-C) and urine ethyl glucuronide (EtG) test. Participants are randomized 1:1 to receive either gabapentin or placebo for 3 months; both arms receive a brief intervention to reduce alcohol use.

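### PEth is analysed only as at or above 50 ng/mL at 3 months, without its measured baseline value; the power this costs depends on the shape of the drug effect

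*Protocol article*

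**What the plan says.** Under Laboratory testing and results, the protocol article says that PEth "is tested at baseline and 3 months". The urine EtG test checks for alcohol at screening. The later urine samples are taken from women to exclude pregnancy. PEth is therefore the only alcohol biomarker the article states after baseline.

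Under Analytic methods, PEth appears among the binary outcomes as "heavy alcohol consumption [defined as PEth ≥ 50 ng/mL". These outcomes follow the primary-outcome approach: logistic regression with the two stratification factors, AUDIT above 20 and clinic site. Any other baseline variable enters only in sensitivity analyses, and only if the arms appear to differ on it. No continuous PEth analysis is stated. ART adherence, by contrast, gets both a binary version and a continuous version. The exploratory longitudinal models also keep heavy alcohol consumption binary, and PEth has only one follow-up time to give them.

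A second drinking outcome exists: self-reported heavy drinking days from the Timeline Followback, analysed as a count by negative binomial regression.

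Under Study outcomes, alcohol consumption is listed first among the outcomes studied "In order to explore potential mechanisms by which gabapentin may lead to HVL suppression".

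**The concern.** PEth is a concentration. A participant who falls from 600 to 150 ng/mL has cut down a great deal, yet scores the same as one who has not changed, because both remain above 50. The baseline concentration is probably a good predictor of the 3-month value, and the planned model does not use it.

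At stake is how a null viral-load result would be read. Lower drinking is the first link in the proposed mechanism. If viral load does not improve, the investigators will want to know whether gabapentin failed to reduce drinking, or whether reduced drinking failed to improve viral load. A weak biomarker test makes that harder to answer.

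**Working it through.** **Inputs from the protocol article.** "The calculations assume an alpha level of 0.05 and that 300 participants are enrolled into the trial"; "assuming 15% loss to follow-up at 3 months (i.e., 255 evaluable subjects"; 1:1 allocation. So 300 × 0.85 = 255, or about 127 per arm. The test is taken as two-sided.

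**Inputs assumed, because the article does not give them.** Log10 PEth mean 2.4 and SD 0.6; correlation between baseline and 3 months r = 0.6; a true fall of 0.20 log10, the same in every participant (10^−0.20 = 0.63, a 37% reduction).

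**The plan's own figure.** The article states no power for PEth. For the primary outcome it claims "80% power to detect an absolute difference of 19% in the proportions with undetectable HVL at 3 months". With 59% against 40% and 255 evaluable, power is 83.3% (normal approximation with continuity correction) or 82.4% (exact enumeration). The difference detectable at 80% is 18.3 to 18.5 points, so 19 is that figure rounded up. This is slightly conservative, is not an error, and has no bearing on PEth.

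**PEth as planned.** The cut is log10 50 = 1.699.
- Control: Φ((2.4 − 1.699)/0.6) = Φ(1.168) = 87.9% above.
- Gabapentin: Φ((2.2 − 1.699)/0.6) = Φ(0.835) = 79.8% above.
- Difference 0.0805. SE = √[(0.8787 × 0.1213 + 0.7982 × 0.2018)/127] = 0.0459. z = 1.75.
- Power = Φ(1.75 − 1.96) = 42%.

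**Log10 PEth with baseline (ANCOVA).** Residual SD = 0.6 × √(1 − 0.6²) = 0.48. SE = 0.48 × √(2/127) = 0.0602. z = 0.20/0.0602 = 3.32. Power = Φ(3.32 − 1.96) = 91%.

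Simulations of the same setting, some with an AUDIT term and values floored at an assumed assay limit of 8 ng/mL, gave 39% to 43% as planned and 90% to 92% for ANCOVA.

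**Varying the assumptions under a uniform shift (same formulas, r = 0.6).**

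| Fall, log10 | Controls ≥ 50 ng/mL | As planned | ANCOVA |
|---|---|---|---|
| 0.20 | 88% | 42% | 91% |
| 0.25 | 88% | 60% | 99% |
| 0.30 | 88% | 77% | >99% |
| 0.20 | 77% | 52% | 91% |
| 0.20 | 63% | 56% | 91% |

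The matching simulations gave 60% to 75% against about 99% for the second and third rows, and 53% to 57% against 90% for the last two.

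A separate calculation in SD units, with 60% to 90% of controls above the cut and r = 0.5 to 0.7, gave a ratio of planned to ANCOVA power of 0.29 to 0.60 for effects of 0.25 to 0.30 SD. The ratio was about 0.53 to 0.77 at 0.40 SD and 0.73 to 0.90 at 0.50 SD.

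**Where the gain comes from.** At 0.20 log10, adding baseline PEth to the binary model raises power from about 40% to 47%. Keeping PEth continuous without baseline gives SE = 0.6 × √(2/127) = 0.0753, z = 2.66 and power 76%. Over 12 simulated settings at 0.25 to 0.30 SD, baseline adjustment of the binary model gained about 3 to 13 points, and keeping PEth continuous without baseline gained about 14 to 33.

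**A different effect shape.** Suppose a fraction of the gabapentin arm falls to about 20 ng/mL and the rest do not change. Two separate simulations gave, as planned against ANCOVA:
- 15% responders: 74% against 64% to 67%.
- 20% responders: 91% to 94% against 87%.
- 20% responders, with a 3-month control mean of 2.1 (one simulation): 67% against 70%.

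Here the cut-off does as well or better.

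**The case against.** The strongest objection is that the size of the loss comes from the assumed effect. A uniform proportional fall suits the continuous model best. If gabapentin works by making a minority nearly stop, the cut-off captures that and the loss disappears. This stands. It rules out saying that the plan halves the power to show reduced drinking, and it rules out saying that the continuous analysis must be the main one. A reader might infer either, but the article gives no PEth mean, SD, correlation or expected effect to support it. Nor does it say what share of controls will be above 50 ng/mL at 3 months. Entry requires a positive EtG, which shows recent drinking and not a PEth level, and both arms receive alcohol counselling, so 88% may be too high.

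Second, the 50 ng/mL outcome stands in a list of examples, and an unseen analysis plan could add a continuous PEth analysis. That is possible. But the article fixes the cut-off, the model and the covariates for PEth, while it gives ART adherence both a binary and a continuous version. This is a stated choice that can be improved, not merely a detail left out.

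Third, a reader might infer that the trial could not tell whether drinking fell. It could still draw on the heavy drinking days count, which is not dichotomised. That count is self-reported, so it complements the biomarker and does not replace it.

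**Conclusion.** The concern holds in a limited form. The stated PEth analysis ignores reductions that end above 50 ng/mL and omits a measured baseline value. Under a uniform 0.20 log10 fall with mean 2.4, SD 0.6, r = 0.6 and 127 per arm, power is about 40% as planned, against 90% for baseline-adjusted log10 PEth. The loss is smaller, and less than half, at 0.25 log10 or more or when 63% to 77% of controls exceed the cut. It vanishes or reverses if the effect is concentrated in 15% to 20% of participants. All of these inputs except the sample size are assumptions.

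The case for baseline adjustment depends less on them: adding baseline log10 PEth to the binary model raised power in every setting examined, though modestly. PEth is a secondary, mechanistic outcome, and the primary viral-load comparison is untouched.

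**What to change.** 1. Add baseline log10 PEth as a covariate to the logistic model for PEth ≥ 50 ng/mL, with AUDIT stratum and clinic.
2. Pre-specify beside it a linear model of log10 PEth at 3 months on arm, baseline log10 PEth, AUDIT stratum and clinic, reported as a ratio of geometric means. Fix a rule for values below the assay limit and check it with a censored regression.
3. State before unblinding which of the two is the main PEth analysis. Because the better choice depends on the expected effect shape, give the reason. Keep heavy drinking days as the second drinking outcome.

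The cost is wording in the analysis plan, one more secondary analysis and a rule for low values; a ratio of geometric means is also less familiar than a proportion. No new test or visit is needed. The article expects recruitment to run to May 2026, so on that timetable the change could be made before unblinding.

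### Negative binomial regression for heavy drinking days, a count capped at about 30, can give wrong model-based standard errors in either direction; robust standard errors should be named

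*Protocol article*

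**What the plan says.** All the relevant text is in the Protocol article. Under Study outcomes, alcohol consumption is the first of the mechanism-related "secondary outcomes: a) alcohol consumption; b) pain severity; c) ART adherence; and d) engagement in HIV care". Under Analytic methods, one measure of it is "Number of heavy drinking days (assessed using the Timeline Followback [TLFB] method) in the past month", which "will be analyzed using negative binominal regression, to account for overdispersion in the data". No standard error type is given for that model, and the upper limit of the count is not mentioned.

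The exploratory longitudinal paragraph of the same section adds: "For number of heavy drinking days, we will use GEE negative binomial regression models". For the GEE of the binary viral load outcome, that paragraph does name the estimator: "standard errors will be based on the empirical-sandwich estimator". The sentence on heavy drinking days does not repeat it.

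The article gives no mean, standard deviation, share of zeros or share at the cap for heavy drinking days, and no power figure for this outcome.

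**The concern.** Overdispersion is a good reason to leave the Poisson model. It does not make the negative binomial variance, mu + alpha × mu², right for days out of about 30. A count confined to 0–30 has variance of at most mu × (30 − mu), a limit the negative binomial does not know. Maximum likelihood chooses alpha to fit the whole shape of the counts, including the zeros, so the variance it implies can be far from the real one. A model-based standard error inherits that error.

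At stake is the reading of one mechanism outcome. Standard errors that are too wide can hide a real reduction in heavy drinking; standard errors that are too narrow can produce a false one. Either would mislead about whether gabapentin acts through alcohol.

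**Working it through.** **Inputs from the article.** "The calculations assume an alpha level of 0.05 and that 300 participants are enrolled into the trial"; "assuming 15% loss to follow-up at 3 months (i.e., 255 evaluable subjects"). Check: 300 × 0.85 = 255, as stated. With 1:1 allocation I used 127 and 128 per arm, and a two-sided test at 5% (the article does not state sidedness). There is no power figure for heavy drinking days to reproduce.

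**Assumptions.** The cap is 30 days. Every shape below is mine, chosen to span what such data might look like.

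**Formulas.** For the log rate ratio in a model with arm only:
- negative binomial, model-based: SE² = (1/m₀ + a)/n₀ + (1/m₁ + a)/n₁, where a is the fitted alpha;
- robust: SE² = s₀²/(n₀m₀²) + s₁²/(n₁m₁²).

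The estimate, log(m₁/m₀), is the same in both; only the standard error changes. With no arm difference, the ratio of the model-based to the true standard error is about √[(mu + a·mu²)/variance].

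**Hand check against simulation** (2,000 null trials per row; a is the median fitted value):

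| Assumed shape | mu | a | True variance | mu + a·mu² | Limit mu(30 − mu) | SE ratio by formula | SE ratio simulated | Type I, model-based | Type I, robust |
|---|---|---|---|---|---|---|---|---|---|
| 40% at 0, 20% at 30, rest uniform 1–20 | 10.191 | 3.148 | 133.3 | 337.1 | 201.9 | 1.59 | 1.63 | 0.1% | 4.0% |
| 20% at 0, 20% at 30, rest uniform 1–20 | 12.283 | 1.346 | 114.8 | 215.4 | 217.6 | 1.37 | 1.39 | 0.4% | 5.1% |
| 40% at 0, 5% at 30, rest geometric | 4.254 | 2.696 | 51.5 | 53.0 | 109.5 | 1.01 | 1.01 | 4.5% | 4.8% |
| 5% at 0, 10% at 30, rest 4–8 days | 8.089 | 0.431 | 56.6 | 36.3 | 177.2 | 0.80 | 0.79 | 11.9% | 5.8% |
| none at 0, 5% at 30, rest Poisson, mean 4 | 5.304 | 0.444 | 35.5 | 17.8 | 131.0 | 0.71 | 0.71 | 17.2% | 5.9% |

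Example, first row: 10.191 + 3.148 × 10.191² = 337.1; 337.1/133.3 = 2.53; √2.53 = 1.59. Here the fitted variance exceeds the largest variance that any 0–30 count with that mean can have (10.191 × 19.809 = 201.9).

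**Other shapes.**
- Beta-binomial on 30 days, mean 3 to 20: SE ratio 0.99 to 1.36, type I error 0.7% to 5.3%.
- Negative binomial counts cut off at 30, mean 3 to 10: SE ratio 1.01 to 1.09, type I error 2.9% to 4.8%.
- Few zeros, 5% to 20% near-daily drinkers: SE ratio 0.65 to 0.92, type I error 7% to 20%.

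**Power, model-based against robust.**
- Beta-binomial, mean 9, within-person clustering 0.5, 30% reduction: 37% against about 61%.
- Second table row, with a tenth of the non-zero participants moved to zero and the share at 30 cut by 40%: 17% against 45%.
- Negative binomial cut off at 30, mean 6: 72% against 73%.

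Where model-based errors are too narrow, power is not a fair comparison, because the test does not hold its level.

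**Robust errors.** Type I error was 4.0% to 5.9% across these scenarios, and about 5% to 7% in a separate set of runs. The Monte Carlo standard error at 5% with 2,000 runs is √(0.05 × 0.95/2000) = 0.5 points.

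**The case against.** A reader might infer that the cap itself makes the standard errors too wide, so that the test is conservative and loses power. The documents do not support that. The result holds for spread or U-shaped counts, but it vanishes for low-mean skewed counts and reverses when zeros are rare and a few people drink almost daily. The trial's population (urine-confirmed recent drinkers, stratified by AUDIT severity, all counselled) makes a wide spread plausible, but nothing in the article selects one shape.

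A reader might also infer that the plan has chosen model-based standard errors. It has not: it is silent, and an analysis plan that is not shown may name sandwich errors, in which case the problem disappears. An article need not list the variance estimator of every secondary model, so silence alone would be no finding. GEE software commonly reports sandwich errors, so the longitudinal model is probably protected, and it is exploratory anyway.

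The consequence is limited too. Alcohol use is also assessed by PEth at 50 ng/mL or above with logistic regression, which this point does not touch.

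These arguments remove any claim about direction and keep the weight modest. They do not remove the point: the article fixes a model whose variance form need not suit the outcome, cites overdispersion as sufficient reason, and does not extend to this model the protection it names for viral load.

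**Conclusion.** The point holds in a direction-neutral form. With model-based standard errors, the planned analysis of heavy drinking days may be conservative, about right or anti-conservative. Over the shapes tried, the standard error ran from 0.65 to 1.63 times its true value, and type I error from 0.1% to about 20% at a nominal 5%. These figures rest on assumed distributions, a cap of 30 days, 127 and 128 participants per arm, a model without covariates, and model-based errors, which the article neither states nor rules out. The outcome is secondary; the primary viral load analysis is unaffected. The change is worth making because the risk runs both ways and one low-cost measure deals with both.

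**What to change.** Under Analytic methods, keep the rate ratio from the log-link model for heavy drinking days, and state that its tests and confidence intervals use robust (sandwich) standard errors. Say the same explicitly for the GEE version, in line with the choice already made for viral load. As a sensitivity analysis, model heavy drinking days out of days assessed (quasi-binomial or fractional logit) with robust errors, which respects the cap.

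The cost is one or two sentences and a software option; no new data are needed, and the estimated rate ratio stays essentially the same. The downside is that the sandwich estimator can be slightly liberal in small samples when a few participants dominate the counts, as the 5% to 7% seen in some runs shows. The change should be fixed before unblinding, so that the choice of standard error cannot depend on the result.
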